## **6.7 Missing Data Diagnostics**

For the mRS, GOSE, SAHOT, CLCE, BICRO and SF-36 endpoints, if more than 15% of patients have missing data for the respective endpoint in either treatment arm at Day 180, the possible impact of these data on the primary analyses will be explored as follows:

- For all endpoints the number of patients with missing data will be summarised. In addition, baseline WFNS score (1-3 v 4-5) will be summarized by treatment arm for each endpoint at each timepoint according to whether data were missing at that timepoint.
- For mRS and GOSE only the analysis at each timepoint will be repeated by carrying forward the outcome from the most recent timepoint with recorded data.

The purpose of these analyses is to assess whether the amount of missing data differs by treatment arm and whether patients with missing data initially had a worse prognosis or were performing worse on other measures recorded at the same timepoint. For example, if there

are more patients in the placebo arm with missing data and those that have missing data were tending to respond less well, this would suggest the treatment effect may have been underestimated.

If the results are marginal for a particular endpoint these investigations may be performed despite neither arm having 15% of patients with missing data. Dependent on results further analyses may be performed to assess the possible impact of missing data.

For TCD endpoints it is not anticipated that missing data could have a bearing on the outcome of the results given the proximity of the measurements to dosing.

Only the year of birth has been recorded. When calculating age, a date of birth of 1st July will be assumed.

## **6.8 Subgroup analyses**

Subgroup analyses will be performed for maximum post-dose MCA mean flow velocity, mRS at 90 days and GOSE at 90 days for the following variables: centre, WFNS score (1-3 v 4-5), Fisher grade, time from ictus (<24h, 24-48h, >48h), Age group ( $\leq 49$ , 50-59,  $\geq 60$ ), gender, surgical procedure (coiling, clipping, not done), location of aneurysm (anterior, posterior), main vessel of aneurysm (anterior, middle, internal, vertebrobasilar) and whether the patient developed a secondary bleed prior to randomisation. Additionally, a subgroup analysis of the primary TCD endpoint will be performed by baseline value split according to quartiles. Results will not be presented for any subgroup level that contains fewer than 10 patients.

Data will be analysed separately for each level of the subgroup. For the primary TCD endpoint, the ANOVA model will be re-run and the treatment effect and associated 95% confidence intervals presented. For mRS and GOSE at 90 days, the logistic regression model will be performed within each level of the subgroup with the odds ratio and associated 95% confidence intervals presented. Results from all subgroups will be presented in a forest plot for each endpoint separately.

If there is evidence of heterogeneity of the treatment effect amongst subgroups the following tests will be performed:

1. A treatment-by-subgroup interaction term will be added to a model containing the terms included in the primary analysis model together with the main effect of the subgroup if not already included in the model. The p-value for the change in model fit by adding the interaction term will be presented
2. A test of the collective heterogeneity amongst subgroups will be performed. This will be achieved by comparing a base model including treatment and all main effects of subgroups with a model containing all two-way interactions of treatment and subgroup. The p-value for the change in model fit by adding all of the interaction terms simultaneously will be presented and described as a global interaction test.

Age will be fitted as a continuous covariate in the interaction tests.

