**Table 1. TCD Recordings**

| Reading                                           | Units/Response |
|---------------------------------------------------|----------------|
| Left Middle Cerebral Artery Mean Flow Velocity    | cm/s           |
| Right Middle Cerebral Artery Mean Flow Velocity   | cm/s           |
| Left Internal Cerebral Artery Mean Flow Velocity  | cm/s           |
| Right Internal Cerebral Artery Mean Flow Velocity | cm/s           |
| Assessment Performed                              | Pre/Post       |
| Lindergaard Ratio Left                            | none           |
| Lindergaard Ratio Right                           | none           |

The primary endpoint is defined as the maximum of all left middle cerebral artery mean flow velocities (MCA-MFV) and right MCA-MFV values recorded after the first dose of randomised therapy including any taken after Day 7.

Baseline values will be defined as:

- The lowest of the left and right MCA-MFV values recorded at the earliest TCD assessment made within 2 days of first dose
- If a patient does not have a TCD recorded within 2 days of dosing, a predicted baseline value will be imputed based on their age, WFNS score (1 to 5), a past medical history of hypertension (yes/no), surgical procedure (clipping, coiling, none), log-CRP and centre as described below.

Amongst patients with baseline values recorded within 2 days of dosing, their baseline value will be regressed on age, WFNS score, hypertension, surgical procedure, log-CRP and centre. The imputed value for patients with a missing baseline value will equal  $\mu + \sum x_{ij}\beta_j$  where  $x_{ij}$  represent the observed values of the  $j$  covariate levels for the  $i^{\text{th}}$  patient and  $\beta_j$  the corresponding parameter estimates from the regression amongst patients with observed baseline values.

Supplementary analyses will also be performed on the mean of the three largest right or left MCA-MFV recorded at any timepoint after dosing. Additionally, an analysis will be performed to describe the effect over time with timepoints grouped, relative to date of Ictus, as Days 3-4, 5-6, 7-9, 10-14, 15-21, 22-28. Within each timepoint the largest MCA-MFV value will be included in the analysis for each patient. For these two analyses, the same baseline as the primary analysis will be used. Using the timepoint analysis the mean effect of Days 5 to 9 will also be estimated.

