***TCD***

The maximum post-dose MCA mean flow velocity and the corresponding baseline value (see Section 5.1) will be summarised according to treatment arm (SFX-01, Placebo) for both the PP and ITT populations. The number of patients who have data imputed at baseline will also be summarised by treatment arm. In addition, the baseline values will be split according to whether they occurred before dosing, on Day1 and Day 2 and summarised by treatment arm.

Results of the statistical analysis will be presented as described in Section 6.4. A graphical presentation of the treatment effects and lsmeans over time will be produced using the results of the MMRM analysis.

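### The baseline-velocity quartile subgroups in SAP 6.8 accept regression-predicted baselines, which fall disproportionately in the middle quartiles and modestly dilute the display

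*SAP*

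**What the plan says.** SAP 5.1 defines the TCD baseline in two steps. The first is the lower of the left and right MCA velocities at the earliest TCD within 2 days of first dose. The second covers patients with no such reading: "If a patient does not have a TCD recorded within 2 days of dosing, a predicted baseline value will be imputed". The model is a single regression among patients with a measured baseline, in which "their baseline value will be regressed on age, WFNS score, hypertension, surgical procedure, log-CRP and centre". As to its form, "The imputed value for patients with a missing baseline value will equal" the intercept plus the sum of covariate values times estimated coefficients. This is a fitted mean, with no residual draw and no multiple imputation.

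SAP 6.8 then plans that "a subgroup analysis of the primary TCD endpoint will be performed by baseline value split according to quartiles". It analyses each subgroup level separately: for the primary TCD endpoint, "the ANOVA model will be re-run and the treatment effect and associated 95% confidence intervals presented". It does not limit the split to measured baselines. Subgroup levels with fewer than 10 patients are not presented.

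Two other places bear on the point. The TCD paragraph of SAP 7 says "The number of patients who have data imputed at baseline will also be summarised by treatment arm", and also splits baseline values into pre-dose, Day 1 and Day 2. SAP 6.7 says "For TCD endpoints it is not anticipated that missing data could have a bearing on the outcome of the results" and plans no missing-data diagnostics for TCD.

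**The concern.** A fitted mean carries only the variance that its model explains. As a linear covariate in the primary ANOVA this does little harm. Cutting the same variable into groups is different. An imputed patient's quartile is then decided by age, WFNS score, hypertension, surgical procedure, CRP and centre, and because predictions sit closer to the centre, the middle quartiles receive too many of these patients. The narrower mixed distribution also pulls the cut-points inward and moves some measured patients.

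At stake is how well the display answers its own question, namely whether the SFX-01 effect varies with starting velocity. Misplaced patients make the quartiles more alike than they should be.

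**Working it through.** **Inputs from the SAP.** 90 evaluable patients (3.1); the imputation covariates and the fitted-mean form (5.1); separate ANOVAs per quartile and the 10-patient minimum (6.8). The SAP states no figure that could be reproduced on this point.

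**Assumptions, because the SAP is silent.** Normal log baseline; baselines missing at random; R-squared of the imputation model mainly 0.1 to 0.3; 5 to 20% imputed (4 or 5, 9 and 18 patients of 90); 4 centres.

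**Step 1: large-sample direction.** With measured baseline variance 1, predicted values have variance R². The outer quartile cut-points lie at ±0.674, so the share of predictions in the two middle quartiles is P(|Z| < 0.674/√R²).

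- R² = 0.1: 0.674/0.316 = 2.13, giving 97%
- R² = 0.3: 0.674/0.548 = 1.23, giving 78%
- R² = 0.5: 0.674/0.707 = 0.95, giving 66%

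The share would be 50% for measured values. The large-sample share in the wrong quartile is 72%, 63% and 53% at these three values, and 48% at R² = 0.6.

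**Step 2: finite sample.** With fewer than 90 patients the coefficients are estimated with error, which spreads the predictions, and the cut-points come from the mixed values. Both weaken the packing. Simulation with the SAP's covariates and 4 centres (800 replicates per cell) gives:

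| Imputed | R² | Imputed in middle quartiles | Imputed in wrong quartile | Measured in wrong quartile | All 90 in wrong quartile |
|---|---|---|---|---|---|
| 5% | 0.1 | 79% | 71% | 3.1% | 6.1% |
| 5% | 0.3 | 69% | 64% | 2.6% | 5.4% |
| 10% | 0.1 | 78% | 72% | 5.5% | 12.1% |
| 10% | 0.3 | 66% | 65% | 4.6% | 10.7% |
| 20% | 0.1 | 73% | 72% | 9.3% | 21.7% |
| 20% | 0.3 | 64% | 64% | 7.5% | 18.7% |

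The last column combines the two before it. For 10% imputed and R² = 0.1: 0.10 × 0.717 + 0.90 × 0.055 = 0.121. A separate simulation on the same assumptions gave 65 to 83% in the middle quartiles and 63 to 71% in the wrong one, so the two agree closely. At 10% imputed the wrong-quartile share falls to 55% at R² = 0.5 and 45% at R² = 0.7.

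**Step 3: effect on the result.** If the treatment effect is linear in true log baseline, the contrast between top-quartile and bottom-quartile effects is attenuated by about 2% at 5% imputed, 5 to 7% at 10% and 10 to 13% at 20%.

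**Step 4: visibility against noise.** 90/4 is 22 to 23 patients per quartile, about 11 per arm. The standard error of one quartile's effect is about √(2/11) = 0.43 SD, and of the difference between two quartiles √2 × 0.43 = 0.60 SD. Attenuation of this size would be hard to see.

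**Step 5: measured baselines only.** Misplacement due to imputation becomes zero. At 5% imputed about 85 patients remain (21 per quartile), at 10% 81 (20) and at 20% 72 (18), all above the minimum of 10. Widening by sample size alone is √(90/85.5) = 1.03, √(90/81) = 1.05 and √(90/72) = 1.12, in line with simulated increases in the SD of the contrast of about 2%, 5% and 10 to 13%.

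**The case against.** The strongest reply is that this is small and partly a matter of preference. The first TCD is due within 48 hours of ictus, readings follow three times a week, and any reading within 2 days of first dose counts, so few baselines may need imputing. The fix removes a bias of a few per cent at the price of intervals wider by a similar percentage. Each quartile ANOVA already estimates about 9 parameters from 22 or 23 patients, so dropping patients also costs residual degrees of freedom. A separate line for imputed patients would be suppressed by the SAP's own minimum at 10% imputed (9 patients). All of this stands, and it sets the size of the point. It does not remove the point: the SAP specifies an imputation model and a count by arm, so it expects some imputation, and nothing in it keeps predicted values out of the velocity quartiles.

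A reader might infer more than the SAP supports:

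- That most imputed patients are certainly in the wrong quartile. This depends on an R-squared that the SAP does not give, and it fails once R-squared exceeds about 0.6.
- That predictions hardly ever reach the outer quartiles. With estimated coefficients, roughly a third do at R-squared 0.3.
- That the primary analysis is compromised or a false subgroup effect created. The primary ANOVA uses the value as a linear covariate, and the imputation model does not use treatment arm. Misplacement therefore dilutes and does not manufacture a treatment difference.
- That the baseline summaries in SAP 7 hide the imputation. Imputed values are counted by arm, and the split into pre-dose, Day 1 and Day 2 should naturally contain measured values only. Just the overall summary mixes the two.

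**Conclusion.** The point holds as a cheap improvement to one exploratory display. Following SAP 5.1 and 6.8 as written assigns patients of unknown velocity to velocity quartiles by their covariates and draws them towards the middle. The mechanism follows from the text; its size rests on the assumed imputed fraction, R-squared, number of centres and missingness at random. Under those assumptions a majority of imputed patients are misplaced, but the resulting dilution of the quartile contrast is at most 10 to 13% at 20% imputed, well within the noise of subgroups this small. No conclusion on the primary endpoint depends on it.

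**What to change.** In SAP 6.8, state that the cut-points, the four quartile subgroups and any interaction test on them use patients with a measured baseline only. Report how many imputed patients were left out by arm, and give them a separate line only if there are at least 10. The all-patient version may be kept as a sensitivity display. Optionally, label the overall baseline summary in the TCD paragraph of SAP 7 as measured values only. Leave the imputed values in the primary ANOVA as planned.

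The cost is a few words in the SAP and intervals in the quartile display wider by about 2%, 5% or 10 to 13% at 5%, 10% or 20% imputed, with slightly fewer residual degrees of freedom per quartile (for example 20 − 9 = 11 in place of 22 − 9 = 13 at 10% imputed).

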#### 3.1 Sample Size

Following protocol amendment 5, the sample size was increased from 90 to up to 120 patients in order to provide 90 who would meet the per protocol criteria and be evaluable for the primary efficacy analysis. Furthermore, this protocol amendment also specified that patients who had potentially received insufficient or incorrect study medication may be replaced.

If the standard deviation is approximately half (53%) of the mean difference in the maximum MCA flow velocity, 90 evaluable patients will have 80% power to detect a statistically significant difference between treatment arms using a 1-sided type 1 error rate of 5%. Statistical significance will be declared if the 2-sided p-value is  $<0.05$ , in this case the trial will have  $>80\%$  power with 90 evaluable patients if the standard deviation is  $<59\%$  of the mean difference.

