## 6 Statistical Methods

### 6.1 General Considerations

All data will be described and analysed according to treatment arm (SFX-01, Placebo) and day and time of assessment (if appropriate), for each patient population (PP, ITT, Safety, sub-study PK).

A (two-sided) significance level of 5% ( $<0.05$ ) will be implemented throughout. The null hypothesis assumed throughout is that there is no difference between the active treatment and the control for any comparison performed (SFX-01 vs Placebo).

Part way through the trial the randomization was amended to stratify by WFNS score (1-3 v 4-5) and centre. For purposes of analyses that are stratified, WFNS score will be taken from the CRFs for patients randomized prior to the amendment and from the random scheme for patients randomized after the amendment.

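### SAP Section 6.8 makes its interaction tests, including the global one, depend on an undefined look at the same subgroup results, so the reported p-values may be selected and cannot be read as ordinary 5% tests

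*SAP*

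**What the plan says.** Section 6.8 names three endpoints: "Subgroup analyses will be performed for maximum post-dose MCA mean flow velocity, mRS at 90 days and GOSE at 90 days". It lists ten factors: centre, WFNS score, Fisher grade, time from ictus, age group, gender, surgical procedure, aneurysm location, main vessel, and secondary bleed before randomisation. For the TCD endpoint there is one more: "a subgroup analysis of the primary TCD endpoint will be performed by baseline value split according to quartiles". Levels with fewer than 10 patients are not presented.

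The model is first fitted separately within each level, and "Results from all subgroups will be presented in a forest plot for each endpoint separately". That display is unconditional. The tests are not: "If there is evidence of heterogeneity of the treatment effect amongst subgroups the following tests will be performed". Two tests follow.

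- A treatment-by-subgroup interaction is added to the primary model, and "The p-value for the change in model fit by adding the interaction term will be presented".
- "A test of the collective heterogeneity amongst subgroups will be performed", by adding all treatment-by-subgroup interactions at once. The SAP calls this a global interaction test.

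Section 6.8 gives no threshold or statistic for the trigger and does not say who judges it. It does not say whether one factor's apparent heterogeneity triggers only its own test or all of them. Section 6.1 sets a two-sided 5% level throughout. By contrast, Section 6.6 adds the EVD-versus-lumbar-puncture interaction for CSF haptoglobin and MDA with no condition.

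**The concern.** The interaction test is the formal evidence on heterogeneity, yet the plan performs it only once heterogeneity has been judged present. The judgement uses the same treatment-by-subgroup estimates that the test then summarises. A p-value that reaches the report only because the estimates already looked different does not have its usual meaning. A reader who sees an interaction p of 0.04 cannot tell how much selection lies behind it.

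The global test is the natural guard against over-reading chance differences among many factors. It sits behind the same trigger, so it may be missing exactly when the report ought to say that nothing stood out overall.

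What is at stake is the reading of effect modification on the primary endpoint and the two key secondary endpoints, and any choice of population for a later trial that draws on it.

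**Working it through.** The SAP states no error rate for the subgroup tests, so there is no figure of its own to reproduce. The check asks what the trigger does when there is no true interaction.

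**Inputs from the SAP.** Two-sided 5% level (Section 6.1). Ten factors on three endpoints plus TCD baseline quartiles (Section 6.8). Ninety evaluable patients, since recruitment was enlarged "in order to provide 90 who would meet the per protocol criteria" (Section 3.1).

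**Assumptions.** 45 patients per arm. A normal outcome with no other covariates. Ten independent factors with assumed numbers of levels and prevalences. Six assumed triggers, because the SAP defines none. There were 4,000 simulated null trials. The Monte Carlo standard error of a 5% rate for the global test is √(0.05 × 0.95 / 4000) = 0.34 percentage points.

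**Number of tests.** 3 × 10 + 1 = 31 single-factor tests at most, counting one analysis population.

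**Direct arithmetic when each factor triggers its own test.** If the trigger amounts to p<a on the same test, with a ≥ 0.05, then P(p<0.05 given run) = 0.05/a:

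- a = 0.5: 0.05/0.5 = 10%
- a = 0.3: 0.05/0.3 = 16.7%
- a = 0.2: 0.05/0.2 = 25%
- a = 0.1: 0.05/0.1 = 50%

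For a two-level factor, running the test when the contrast exceeds 1 SE corresponds to a = 2(1−Φ(1)) = 0.317, giving 0.05/0.317 = 15.8%.

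**Simulation under both readings.** In the visual rule, the estimates for two levels differ by more than the smaller of their confidence-interval half-widths. The last three columns take the reading in which any factor's heterogeneity triggers all tests.

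| Assumed trigger | Own test only: share of tests run | Own test only: P(p<0.05 given run) | Triggers all: share of trials in which tests run | Triggers all: single-factor P(p<0.05 given run) | Triggers all: global P(p<0.05 given run) |
|---|---|---|---|---|---|
| Visual | 40.1% | 12.4% | 99.5% | 5.2% | 5.2% |
| p<0.5 | 49.9% | 10.3% | 99.9% | 5.2% | 5.2% |
| p<0.3 | 30.3% | 17.0% | 97.4% | 5.3% | 5.3% |
| p<0.2 | 20.2% | 25.5% | 90.1% | 5.7% | 5.7% |
| p<0.1 | 10.1% | 50.9% | 66.1% | 7.8% | 7.6% |
| p<0.05 | 5.2% | 100% | 41.0% | 12.6% | 11.0% |

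**Unconditional error.** When each factor triggers its own test, the chance that a given test is run and gives p<0.05 is 5.0% to 5.2% for every trigger.

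**Non-triggering factors.** If any factor triggers all tests, the factors that did not set off the trigger have a median p of 0.53 to 0.75, against 0.50 without a trigger. Their p-values are shifted upwards.

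**Without the condition.** P(p<0.05) is 5.2% per single-factor test (median p 0.50) and 5.2% for the global test. Multiplicity remains. If the tests were independent, the chance of at least one p<0.05 would be 1 − 0.95^10 = 40% for ten tests, 1 − 0.95^11 = 43% for the eleven TCD tests and 1 − 0.95^31 = 80% for all 31. The expected number is 31 × 0.05 = 1.55.

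**The case against.** The strongest defence is that the trigger sentence can be read as one trigger for the whole set. It speaks of heterogeneity among subgroups in general, and the list it opens includes a single test over all factors. On that reading, with any loose rule, the tests are run in 90% or more of null trials and their p-values are close to nominal. This stands: the wording does not settle the matter, and on this reading the harm is small unless the rule is strict.

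The factors and endpoints are also fixed in advance, and the forest plots appear whatever happens, so selection is partly visible. That stands too, although separate intervals for each level do not replace an interaction test. The study is Phase II with exploratory efficacy aims, and no decision rule hangs on these p-values. That limits the weight of the point.

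Three stronger readings are tempting, and the documents support none of them.

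- A reader might infer that every reported interaction p-value is too small. Each one is calculated correctly. The distortion is conditional on the test being reported, and it can run upwards for factors that did not set off the trigger. The Section 6.6 interaction is not selected at all.
- A reader might infer that the type I error of each test is inflated. Unconditionally it stays at about 5%.
- A reader might take the 10% to 26% as a property of this plan. It follows from assumed cut-offs under one reading. For age, the trigger and the test are not even the same statistic, because age is plotted in three groups but tested as continuous.

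**Conclusion.** The point holds for Section 6.8 and is minor. The trigger for both the single-factor tests and the global test is undefined and rests on the results being tested, so a reported p-value cannot be taken as an ordinary 5% test. The distortion runs from almost nil to large according to a rule that the SAP does not write down, and this uncertainty is itself the reason to change the sentence.

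The figures rest on a simulated normal outcome, independent factors and assumed levels, prevalences and triggers. They were not run for the proportional odds models used for mRS and GOSE.

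**What to change.** In Section 6.8, delete the condition. Fit and report the treatment-by-subgroup interaction p-value for every listed factor on maximum MCA velocity, mRS at 90 days and GOSE at 90 days, and for baseline quartiles on the TCD endpoint. Report the global interaction test once for each endpoint. Place the p-values beside the forest plots, label them exploratory and unadjusted, and state how many were computed (up to 31 single-factor tests).

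The cost is an edit to one paragraph and a few more model fits, with no new data. Removing the trigger does not remove multiplicity: between one and two of 31 p-values would fall below 0.05 by chance, and the report should say so.
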